**Fig. 2 Fig2:**
[figure not shown]
Flow chart of the procedures that participants will undergo

### Interventions: treadmill-based C-Mill therapy and the overground FALLS program

C-Mill therapy is a structured treadmill training program with a specific emphasis on practicing walking adaptability (as detailed in Table 1 and Additional file 1), using gait-dependent augmented-reality content projected on the instrumented treadmill surface to elicit step adjustments [1, 13–15, 25–28]. Figure 3 shows various exercises of C-Mill therapy, including exercises to practice avoidance of projected visual obstacles (Fig. 3a), exercises to practice accurate foot placement on a step-to-step basis by walking to a regular or irregular sequence of visual stepping targets (Fig. 3b), exercises to practice acceleration and deceleration by maintaining position within a projected walking area that moves along the treadmill (Fig. 3c), and a functional and interactive walking adaptability game (Fig. 3d). C-Mill therapy is a patient-tailored type of training in that the therapist can adjust the difficulty of the different exercises by manipulating content parameters as the obstacle size and available response time for obstacle negotiation, the variation in the sequence of stepping targets, and the degree of acceleration and deceleration of the moving walking area. As progressive training has previously been shown to have beneficial effects [29–31], therapists are instructed to increase the difficulty of C-Mill exercises as tolerated by the participant, by either changing content parameters or increasing the belt speed, as described in the pre-defined training protocol (Table 1). To assist therapists in progressively scaling the C-Mill therapy sessions, the participant’s perceived fear and difficulty levels during the sessions will be assessed at a scale from 0 (no fear or not difficult) to 10 (much fear or very difficult), as well as their rating of perceived exertion using the Borg scale (range 6–20, [32]). Furthermore, the pre-defined protocol will guide therapists to vary C-Mill exercises, both in terms of content and the order in which the exercises will be performed, inspired by recent insights into motor learning showing superior transfer and retention effects with variability in practice [16]. C-Mill therapy will be performed in groups of two persons with stroke supervised by one therapist. Therapy sessions will last 1.5 hours each, divided in exercise blocks of 3–8 min, during which the participants alternately train and rest (Table 1).

**Table 1 Tab1:** Pre-defined protocol for treadmill-based C-Mill therapy

Setting	Groups of two participants for 90 min; participants will alternately train and rest.
Frequency	Twice weekly treadmill training program with specific emphasis on walking adaptability.
Therapy	In the first week, a combination of obstacle avoidance (avoiding visual obstacles projected on the treadmill), practice of accurate foot placement on a step-to-step basis (walking to a regular or irregular sequence of visual stepping targets), and a functional and interactive walking adaptability game (game with the theme ‘beach’ or ‘forest’) will be performed. In weeks 2–5, the combination of obstacle avoidance, accurate foot placement on a step-to-step basis and the functional and interactive walking adaptability game will be complemented by walking speed adaptations (acceleration and deceleration evoked by a moving walking area).
	Participants will start in week 1 at a comfortable walking speed; this speed will be gradually increased during the 5 week period. The weekly increase of the walking speed will be 10 %, provided that the therapy remains safe and is tolerated by the participant. Besides the walking speed, the difficulty of C-Mill exercises will be gradually increased, as tolerated by the participant.
Therapist	C-Mill therapy will be provided by a single therapist, an expert in C-Mill therapy. The therapists involved in the C-Mill therapy were all trained with regard to operating the C-Mill and to the specific guidelines of the intervention before the study started. Most therapists were already experienced C-Mill users before the study started. The therapists regularly meet the research assistant to ensure adherence to the protocol (Additional file 1).

**Fig. 3 Fig3:**
[figure not shown]
Exercises of treadmill-based C-Mill therapy: (**a**) obstacle avoidance; (**b**) visually guided stepping to a sequence of stepping targets; (**c**) acceleration and deceleration evoked by a moving walking area; (**d**) functional and interactive walking adaptability game (adopted from Van Ooijen et al. [20])

The FALLS program [9] is an overground therapy program aimed at reducing the number of falls in people with stroke by practicing walking adaptability, among other aspects (as detailed in Table 2 and Additional file 2). Figure 4 shows various exercises of this pre-defined FALLS program, including exercises to practice obstacle avoidance (Fig. 4a), exercises to practice foot placement while walking over uneven terrain (Fig. 4b), tandem walking (Fig. 4c), and slalom walking (Fig. 4d). These exercises must also be performed while cognitive and motor dual-tasks are imposed, as well as under visual constraints. In addition, the program incorporates exercises to simulate walking in a crowded environment and to practice falling techniques (one session per week). The FALLS program was originally performed in groups of six persons with stroke, with two or three therapists per group in therapy sessions lasting 2 hours each [9]. Following design considerations for this study (as detailed in the next section), the FALLS program will be performed in groups of four to six persons with two or three therapists per group, with sessions lasting 1.5 hours, including rest.

**Table 2 Tab2:** Pre-defined protocol for the overground FALLS program

Setting	Groups of 4–6 participants for 90 min, participants will alternately train and rest.
Frequency	Twice weekly overground training program, which incorporates walking adaptability exercises.
Therapy	The first therapy session of the week will be devoted to an obstacle course that simulates potential challenging situations of daily life. The obstacle course facilitates practicing balance, gait, and coordination, and mimics activities of daily life with high fall risk, such as walking over obstacles, uneven terrain, slalom walking and tandem walking. The obstacle course will also be negotiated while imposing cognitive and motor dual-tasks, as well as under visual constraints.
	The second therapy session of the week will include walking exercises and practice of fall techniques. The walking exercises simulate walking in a crowded environment. Adjustments in walking speed and direction are required during these exercises and collisions with other people challenge balance. The practice of fall techniques is based on martial arts techniques and will include falling forwards, backwards, and laterally. The level of difficulty will be gradually enhanced by increasing fall height (from sitting on a safety mat to stance height).
Therapist	The therapy sessions will be provided by two or three therapists, depending on the size of the group. At least one of therapists is trained in the background, methods, and techniques of the FALLS program. All therapists involved in the FALLS program are trained and experienced with regard to the program protocol and instructed to follow the specific guidelines of the intervention for the purpose of this trial. The therapists regularly meet the research assistant to ensure adherence to the protocol. (Additional file 2).

**Fig. 4 Fig4:**
[figure not shown]
Exercises of the obstacle course of the overground FALLS program: (**a**) obstacle avoidance; (**b**) walking over uneven terrain; (**c**) tandem walking; (**d**) slalom walking

Both interventions are matched for therapy duration (90 min), frequency (twice weekly) and therapist attention (mean participant-to-therapist ratio, 2:1). The amount of walking practice per session (defined as the number of steps performed during therapy sessions) will be compared between the two interventions and treated as the process measure. Therefore, the number of steps taken during C-Mill therapy sessions will be registered using the treadmill’s inbuilt step counter, while an observer will count the number of steps taken during the FALLS program offline in a random selection of FALLS program sessions using video recordings of the sessions in question.

Finally, after completing the last session of the intervention, participants will be asked to fill in a purpose-designed questionnaire to register perceived discomfort during and after therapy sessions, as well as their experience with the therapy, to compare the feasibility of the interventions from a participant’s perspective.

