### Sample size

The primary outcome measure in this study will be walking speed. Previous clinical trials in people with stroke by Yang et al. [49] and Jaffe et al. [50] showed greater improvements in walking speed after treadmill training in a complex and challenging virtual reality environment than after, respectively, conventional treadmill training and overground obstacle-avoidance training [49, 50]. Unfortunately, effect sizes and required sample sizes for a controlled clinical trial with multiple comparisons cannot be estimated from the results of these studies, but both reported significant between-group differences in walking speed with small sample sizes of 9 to 10 participants in each intervention group. The study of Yang et al. [49] allows for a sample size calculation for post-hoc analyses for significant group effects on walking speed with independent *t* tests. Based on those results, we aim for a relative, clinically relevant, improvement in walking speed of 0.50 km/h (*∆*) with a common standard deviation (*SD*) of 0.47 km/h, which results in a sample size of 14 participants in each group to achieve 80 % power with a two-tailed *α* of 0.05, i.e., following$$ N=\frac{2S{D}^2{\left({Z}_{\alpha }+{Z}_{\beta}\right)}^2}{\varDelta^2} $$[51]. Considering a drop out of 10–25 %, we chose to increase our sample to 20 participants in each intervention group to be on the safe side for establishing the relative efficacy of the two interventions in terms of improvements in walking speed.

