### Data analysis

Descriptive group statistics will be used to characterize the two intervention groups in terms of sex, age, height, body mass, Mini-Mental State Examination, Functional Ambulation Category, medication use, co-morbidities, side and location of the lesion, current living situation, daily functioning and the use of assistive devices, as well as perceived discomforts during and after therapy sessions and participant’s experience with the therapy. An independent *t* test will be used to compare the mean number of steps taken per session between the two interventions.

Primary and secondary longitudinal outcome measures that are normally distributed will be analyzed using repeated-measures ANOVA with the between-subject factor group (two levels: C-Mill therapy and the FALLS program) and the within-subject factor time (four levels: pre-intervention [T0], post-intervention [T1], retention [T2], and follow-up [T3] tests). Post-hoc analysis using independent *t* tests between groups per time level will be performed in case of significant interaction effects. For ordinal or non-normal distributed variables, we will use Mann–Whitney *U* tests and Friedman tests to evaluate possible main effects of group and time, respectively. To analyze possible interactions between groups and times, we will apply Kruskal–Wallis tests to change scores (i.e., relative to the previous time level) at T1, T2, and T3. When significant, Mann–Whitney *U* post-hoc tests will be performed to identify between-group differences in change scores per time level. Significant effects are assumed for *P* < 0.05. Data will be analyzed as randomized. Missing data will be imputed using the data from the last available measurement.

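### The questionnaire meant to compare feasibility is tied to completing the last session, so as written the comparison covers completers only and can understate discomfort in an arm that loses participants because of it

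*Protocol article*

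**What the plan says.** The closing paragraph of the Interventions section sets one time point for the participant questionnaire: "after completing the last session of the intervention, participants will be asked to fill in a purpose-designed questionnaire to register perceived discomfort" and experience with the therapy. The same sentence states what it is for: "to compare the feasibility of the interventions from a participant’s perspective".

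The Data analysis section places the answers among the descriptive group statistics, "as well as perceived discomforts during and after therapy sessions and participant’s experience with the therapy". No test is planned for them, and the questionnaire is not among the primary and secondary outcomes in Table 3. The same section adds two general rules: "Data will be analyzed as randomized" and "Missing data will be imputed using the data from the last available measurement".

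The only other participant-reported tolerability data in the article are ratings made during therapy. In the description of C-Mill therapy, "the participant’s perceived fear and difficulty levels during the sessions will be assessed at a scale from 0" to 10, together with a Borg exertion rating. Their stated role is to help therapists scale the sessions. The article describes no counterpart for the FALLS program.

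The Sample size section allows for 10–25 % drop-out and sets 20 participants per group.

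**The concern.** Stopping therapy because of discomfort or fear is itself evidence on feasibility. If the form is given only on completing the program, the measure of discomfort is conditioned on having tolerated the therapy, and those who tolerated it least are missing from the answers.

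The selection need not be the same in both arms, because the programs differ in content that might lead someone to stop. Table 2 includes practice of falling from progressively greater height and collisions with other people. Table 1 includes a weekly increase in walking speed, as far as it is safe and tolerated. If stopping differs by arm, the two groups of completers are no longer comparable, and the distortion could favor either program.

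What is at stake is the interpretation of one stated comparison, feasibility as participants see it. No analysis plan can recover answers that were not collected.

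**Working it through.** **1. The plan's own figure.** Inputs from the Sample size section: difference 0.50 km/h, SD 0.47 km/h, two-sided α 0.05, power 80 %.

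N = 2 × 0.47² × (1.960 + 0.842)² / 0.50² = 13.87, rounded up to 14 per group, as stated.

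Allowing for drop-out: 14 / 0.90 = 15.6, so 16; 14 / 0.75 = 18.7, so 19. Twenty per group covers the range. Nothing in this point disputes the sample size.

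**2. Can another rule or record fill the gap?**
- *Analysis as randomized* decides the arm in which a response is counted. It does not create a response.
- *Carrying forward the last measurement* needs an earlier value. A form given once has none.
- *In-session ratings* are described for C-Mill only and serve to adjust the therapy, so as described they cannot support a comparison between arms.
- *Table 3* lists no other measure of discomfort with the therapy.

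**3. How many could be missed?** 10 % of 20 = 2 and 25 % of 20 = 5 per arm, that is 4 to 10 of 40, leaving 18 to 15 completers per arm. Under the plan's own allowance this is an upper bound. The Study design section puts the last test 12 months after therapy, while the questionnaire falls at the end of a 5-week program. Anyone lost after that has already been asked. The article does not say how the drop-out divides between the two periods.

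**4. How far could the result move?** One person is 1/20 = 5 percentage points of an arm of 20. The documents give no discomfort rate and no scoring for the form, so the following is an illustration. Assumptions:
- all 20 start therapy;
- responses can be read as discomfort yes or no;
- 20 % of completers report discomfort;
- k people stop because of discomfort;
- anyone stopping for another reason has the completers' rate.

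Share among all who started = [0.20 × (20 − k) + k] / 20

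| k | Share among all starters | Share seen in completers |
|---|---|---|
| 0 | 4.0/20 = 20 % | 20 % |
| 1 | 4.8/20 = 24 % | 20 % |
| 2 | 5.6/20 = 28 % | 20 % |
| 3 | 6.4/20 = 32 % | 20 % |
| 4 | 7.2/20 = 36 % | 20 % |
| 5 | 8.0/20 = 40 % | 20 % |

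Each person who stops because of discomfort moves the share by 5 − 1 = 4 points net, because a 20 % expectation is replaced by a certain yes. If nobody stops for that reason, there is no shift. The comparison between arms is distorted only to the extent that k, or the completers' mix, differs between them.

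**The case against.** The strongest reply is that this is a peripheral item in a condensed article. The aim in the Background section concerns effects on walking speed, walking adaptability and clinical measures, not feasibility. The questionnaire is summarized descriptively, with no hypothesis or test, and no trial conclusion rests on it. That stands, and it limits the weight of the point.

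A second reply is that the article gives the usual timing of the form and nowhere says that people who stop are excluded. The full protocol, or the additional files with the intervention guidelines, may deal with them. *Last session* might also be stretched to mean the last session attended. This stands in part: that early stoppers are not asked is an inference from the stated trigger. But the trigger is stated, completing the program's last session is its natural meaning, and followed as written it selects completers. If the sponsor meant otherwise, one clarifying sentence settles it.

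A third reply concerns size, and it stands. A reader might infer that 2–5 participants per arm will go unasked. The drop-out allowance does not support this, since it covers a trial running to 12 months after therapy. A reader might also infer that a real difference of 28 % against 40 % would be reported as 20 % against 20 %. That requires all drop-out to fall within the 5 weeks, all of it to be due to discomfort, and the arms to sit at opposite ends of the range. The documents support none of these.

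**Conclusion.** The point holds within limits. As written, the only instrument described for comparing feasibility between the arms is given at a moment that early stoppers do not reach, and neither the general analysis rules nor the in-session ratings make up for it. The descriptive comparison is therefore one of completers. It understates discomfort in an arm whenever those who stop have more discomfort than those who finish.

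The size cannot be stated from the documents. At most 2–5 of 20 per arm are affected under the plan's drop-out allowance, and probably fewer if part of the drop-out falls in follow-up. Each person stopping because of discomfort is 5 percentage points of an arm of 20, and the shift could be nil.

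Two stronger readings go too far. One is that the arm with more losses would look the more tolerable: in the illustration the arms merely look equal, and a reversal would also need its completers to report less discomfort than those of the other arm. The other is that the main results are in doubt: the primary and secondary outcomes and the sample size are untouched. The change is worth making because it is cheap and rescues a stated comparison.

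**What to change.** Change the trigger in the Interventions section:
- Every participant who started therapy gets the same questionnaire, at the last session or at the time of stopping, by phone or post if they do not return.
- The reason for stopping is recorded where it is known.

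In the Data analysis section, report the responses by randomized arm beside the numbers completing, stopping (with reasons) and not responding. Do not impute a negative response for people who cannot be reached. Their reason may be unknown, and the table of stops and reasons already shows what is known.

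The Trial status section says that recruitment is ongoing. For anyone who stopped before the change, state how many were not asked.

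Cost: about one sentence in each section, and at most 4–10 forms given earlier or remotely under the plan's drop-out allowance. No new visit, instrument or staff is needed. The drawback is that a few responses will be collected remotely and will reflect fewer sessions, so the report should identify them.

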### Outcome measures

After group allocation, pre-intervention tests will be performed to assess the baseline values of primary and secondary outcome measures and to collect participant characteristics (sex, age, height, body mass, medication use, co-morbidities, side and location of the lesion, current living situation, daily functioning and the use of assistive devices). The primary outcome measure in this study will be walking speed. Walking speed will be assessed using the 10 Meter Walking Test [33], which has been shown to be a reliable and robust means for measuring walking speed [34].

The secondary outcome measures are inspired by the targeted-stepping and obstacle-avoidance results of Hollands et al. [35] and Van Ooijen et al. [15], underscoring the importance of task-specificity and context-specificity in walking adaptability assessments. Van Ooijen et al. [15] showed enhanced obstacle-avoidance success rates at lower attentional costs after a period of C-Mill walking adaptability therapy, while Hollands et al. [35] showed that measures of targeted stepping were clinically meaningful components in the recovery of functional mobility after stroke. Therefore, the 10 Meter Walking Test will also be performed in combination with context (10 Meter Walking Test with three obstacles, a tandem walking path and three stepping targets) (Fig. 5), a cognitive dual-task (10 Meter Walking Test while counting backwards in steps of three [36]) and both context and dual-task (10 Meter Walking Test with three obstacles, a tandem walking path, and three stepping targets, and while counting backwards in steps of three). Walking adaptability will also be assessed using the Interactive Walkway (Technology4Science, Vrije Universiteit Amsterdam, The Netherlands), a walkway instrumented with multiple Microsoft Kinect for Windows sensors and a projector to present visual context, such as obstacles and stepping targets in a gait-dependent manner (Fig. 6). The walking adaptability evaluation with the Interactive Walkway includes targeted-stepping assessments, obstacle-avoidance assessments, and obstacle-avoidance assessments while counting backwards in steps of three. The obstacle-avoidance assessment of the Interactive Walkway differs from the 10 Meter Walking Test with context in that the Interactive Walkway obstacles can be suddenly presented in a gait-dependent manner, that is, the obstacle suddenly appears at the location where the participant would place his or her foot without adjusting gait. Hence, a step adjustment is always required to avoid the obstacle successfully. Moreover, this step adjustment needs to be performed under high time-pressure demands, which is especially difficult for persons after stroke [37]. The difference between the stepping targets within the 10 Meter Walking Test with context and the Interactive Walkway targeted-stepping assessment is that the Interactive Walkway targets are presented in regular and irregular sequences of visual stepping targets based on participants’ self-selected step length. In this way, it is possible to evaluate foot placement errors on a step-to-step basis for each participant. The 10 Meter Walking Test scores and Interactive Walkway assessment scores will be given in seconds required to complete each test, as well as in the number of errors made during the obstacle crossings, targeted stepping, and tandem walking. The cognitive dual-task, a serial-3 subtraction task, will be analyzed by counting the number of subtractions, as well as the number of mistakes made (dual-task performance [DTP]). Subtraction-task performance while walking will be normalized to subtraction-task performance while sitting (i.e., single-task control condition). These walking adaptability evaluation tools are expected to be sensitive and specific for finding improvements after walking adaptability interventions.

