**Fig. 6 Fig6:**
[figure not shown]
Walking adaptability assessments using the Interactive Walkway: (**a**) avoidance of suddenly appearing obstacles and (**b**) walking to a sequence of stepping targets, both presented on the walking surface in a gait-dependent manner

Secondary outcome measures are drawn from a comprehensive set of common clinical measures to determine walking ability, balance, and other walking-related constructs, including Timed Up-and-Go test [38] and Functional Ambulation Category [23]. The obstacle-avoidance subtask of the modified Emory Functional Ambulation Profile will be performed [39], a conventional clinical test closely related to the construct of walking adaptability. The modified Emory Functional Ambulation Profile is reliable and valid for use in people with stroke [40]. Balance will be assessed using the Berg Balance Scale, which provides a psychometrically sound measure of balance impairment for use in post-stroke assessment [40, 41]. Executive function will be assessed using the valid and reliable Trail Making Test [42]. Balance confidence will be assessed with the Activities-specific Balance Confidence scale, a questionnaire measuring balance confidence in performing specific activities, which has good test-retest reliability and validity [43, 44]. Self-reported limitations in walking will be assessed using the Walking Questionnaire [45], which targets experienced limitations in indoor and outdoor walking relative to pre-stroke walking limitations. Finally, the Nottingham Extended Activities of Daily Living scale [46–48] will be used to assess activities of daily living. Table 3 provides an overview of the tests that will be performed at T0, T1, T2 and T3.

**Table 3 Tab3:** Overview of all tests performed at T0, T1, T2 and T3

Primary outcome measure
10 Meter Walking Test (m/s)
Secondary outcome measures
10 Meter Walking Test with context (m/s, number of errors)
10 Meter Walking Test with a cognitive dual-task (m/s, DTP)
10 Meter Walking Test with context and a cognitive dual-task (m/s, number of errors, DTP)
Interactive Walkway targeted-stepping assessment (m/s, number of errors)
Interactive Walkway obstacle-avoidance assessment (m/s, number of errors)
Interactive Walkway obstacle-avoidance assessment with a cognitive dual-task (m/s, number of errors, DTP)
Timed Up-and-Go test (m/s)
Functional Ambulation Category (3–5)
Obstacle-avoidance subtask of the modified Emory Functional Ambulation Profile (m/s)

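### Dual-task performance is worded as a count over a fixed-distance walk with no scaling by time, so the count depends on walking speed as well as on cognition

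*Protocol article*

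**What the plan says.** The Outcome measures section adds a serial-3 subtraction task to some walking tests, one of them described as "10 Meter Walking Test while counting backwards in steps of three". The task "will be analyzed by counting the number of subtractions, as well as the number of mistakes made"; the article labels this dual-task performance (DTP). The next sentence adds: "Subtraction-task performance while walking will be normalized to subtraction-task performance while sitting". The sitting condition serves as the single-task control. Its duration is not given, and the text does not say whether the normalization uses counts or rates.

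The same section says that the walking-test scores "will be given in seconds required to complete each test", so test duration varies with the participant's speed. Table 3 lists DTP beside speed, for example "10 Meter Walking Test with a cognitive dual-task (m/s, DTP"), and attaches no time unit to DTP. It appears in three secondary outcomes: the 10 Meter Walking Test with dual-task, the same test with context and dual-task, and Interactive Walkway obstacle avoidance with dual-task.

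**The concern.** Over a fixed distance, the time available for subtracting is distance divided by speed. A count of responses therefore mixes how fast the participant subtracts with how long the walk lasts. Speed is the quantity that both interventions aim to raise and on which the trial expects the arms to differ, so this nuisance factor is tied to the effect under study.

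The two components mislead in opposite directions. If a participant walks faster and subtracts at the same rate with the same accuracy, there are fewer subtractions, which looks like a loss, and fewer mistakes, which looks like a gain. Neither reflects a change in cognitive performance. The article motivates its dual-task tests by earlier findings of lower attentional cost after C-Mill therapy, so the cognitive side of this trade-off needs a score that can be read on its own.

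**Working it through.** **Inputs from the article**
- Distance of the walking test: 10 m (Outcome measures).
- Target difference in walking speed: "improvement in walking speed of 0.50 km/h" (Sample size), which is 0.50 / 3.6 = 0.139 m/s.

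**Assumptions, not in the article**
- Starting dual-task speeds of 0.5, 0.7 and 1.0 m/s, with 0.4 to 1.2 m/s as a wider range.
- Subtraction rate and accuracy unchanged.
- The primary-outcome target carried over to dual-task walking, for which the article gives no target.

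**Step 1. The plan's own figure.** The only computed figure in the article is the sample size. Its formula gives 2 × 0.47² × (1.960 + 0.842)² / 0.50² = 13.87, rounded up to the stated 14 per group. It reproduces. It matters here only as the source of the 0.50 km/h.

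**Step 2. Effect of speed on the raw count.** With subtraction rate r and speed v, count = r × 10 / v. After a gain d, the ratio of new to old count is v / (v + d), whatever r is.

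| Starting speed (m/s) | Walk time before → after (s) | Count ratio | Change |
|---|---|---|---|
| 0.5 | 20.0 → 15.7 | 0.783 | −22% |
| 0.7 | 14.3 → 11.9 | 0.834 | −17% |
| 1.0 | 10.0 → 8.8 | 0.878 | −12% |

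Over the wider range the change runs from −25.8% (0.4 m/s) to −10.4% (1.2 m/s). The expected number of mistakes falls by the same percentage.

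**Step 3. Does the sitting normalization remove it?** Assume 0.8 m/s, 0.4 subtractions per second walking and 0.5 per second sitting. The walk shortens from 12.5 to 10.65 s.
- Walking count over the count from an assumed fixed 30 s of sitting: (0.4 × 12.5) / (0.5 × 30) = 5.0 / 15 = 0.333 before, and 4.26 / 15 = 0.284 after. Change: −14.8%, the same as the raw count.
- Rate over rate: 0.4 / 0.5 = 0.80 before and after. Change: 0%.
- Sitting period matched to each walk's own duration T: (0.4 × T) / (0.5 × T) = 0.80. Change: 0%.

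If 10% of responses are mistakes, the mistake count falls from 0.50 to 0.43, although accuracy is the same.

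**Step 4. Between arms.** With equal subtraction rates, the ratio of the C-Mill count to the FALLS count is v(FALLS) / v(C-Mill). Starting from equal speeds, equal gains leave this at 1, so the artefact then appears in the time effect and not between arms. Only a difference in dual-task speed gain distorts the comparison.

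**Step 5. What would offset it.** To keep the count constant, the subtraction rate must rise by d / v: 34.7% from 0.4 m/s, 13.9% from 1.0 m/s and 11.6% from 1.2 m/s.

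**The case against.** The strongest reply is that the article is silent here, not wrong. It names the raw data and the principle of comparison with sitting, and the exact formula for a secondary score is often left to a fuller document. If the normalization divides rate by rate, the artefact vanishes, as Step 3 shows. The section also describes walking scores in seconds where Table 3 gives m/s, so its wording may describe data capture and not the analysis scale.

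Part of this stands: a speed-driven bias in the final score is possible but not established. What remains is that the article does state how the task is analyzed, and states it as counts. The normalization sentence refers to performance just defined that way, and nothing in the text or Table 3 turns it into a rate.

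The reply is also right on scale. DTP is a component of three of the 14 secondary outcomes listed in Table 3. Each of those rows also reports speed, so a reader could view the two together.

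Three stronger readings are tempting and not supported:
- A reader might infer that the score falls in precisely the arm that improves. Both arms may gain speed, the mistake count moves in that arm's favour, and a real rise in subtraction rate could offset the fall.
- A reader might apply the fixed 10 m to all three DTP outcomes. The Interactive Walkway distance is not given.
- A reader might extend the point to targeted-stepping errors, because targets are set from each participant's step length. The number of targets is not stated and the mechanism is different, so that is conjecture.

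**Conclusion.** The point holds in limited form. As worded, DTP is a count over a walk whose duration shortens as speed rises, and the stated normalization does not clearly correct for this. Under the assumptions listed, the subtraction count falls by about 12% to 22% for starting speeds of 1.0 down to 0.5 m/s, with no change in cognition.

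This applies to the two 10 Meter Walking Test dual-task outcomes, and to the Interactive Walkway dual-task outcome if its distance is also fixed. The size and direction of any between-arm distortion depend on the difference in dual-task speed gain, which the article does not give. The primary outcome and the sample size are unaffected.

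**What to change.** Define DTP as correct subtractions per second while walking divided by correct subtractions per second while sitting, and report mistakes as a proportion of responses. State the duration of the sitting condition. Because this definition divides by each test's own time, it serves the Interactive Walkway outcome as well, whatever its distance.

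The cost is a change of wording and some rescoring. Completion times are already planned for every test, so participants already assessed can be rescored, provided their sitting duration is known. If rates were intended all along, one sentence settles the matter.

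The drawback is coarseness. Few responses fit into 10 m for fast walkers: at an assumed 1.2 m/s and 0.4 subtractions per second, 8.33 s × 0.4 gives about 3.3 responses, so a single mistake moves the proportion by about 30 percentage points (1 / 3.33).
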